## Abstract

**Background:**

The optimal management of acute cervical spinal cord injury (SCI) associated with preexisting canal stenosis remains to be established. The objective of this study is to examine whether early surgical decompression (within 24 hours after admission) would result in greater improvement in motor function compared with delayed surgery (later than two weeks) in cervical SCI patients presenting with canal stenosis, but without bony injury.

**Methods/design:**

OSCIS is a randomized, controlled, parallel-group, assessor-blinded, multicenter trial. We will recruit 100 cervical SCI patients who are admitted within 48 hours of injury (aged 20 to 79 years; without fractures or dislocations; American Spinal Injury Association (ASIA) grade C; preexisting spinal canal stenosis). Patients will be enrolled from 36 participating hospitals across Japan and randomly allocated in a 1:1 ratio to either early surgical decompression (within 24 hours after admission) or delayed surgery following at least two weeks of conservative treatment. The primary outcomes include: 1) the change from baseline to one year in the ASIA motor score; 2) the total score of the Spinal Cord Independence Measure and 3) the proportion of patients who are able to walk without human assistance. The secondary outcomes are: 1) the health-related quality of life as measured by the Medical Outcomes Study Short Form 36 and the EuroQol 5 Dimension; 2) the Neuropathic Pain Symptom Inventory and 3) the walking status as evaluated with the Walking Index for Spinal Cord Injury II. The analysis will be on an intention-to-treat basis. The primary analysis will be a comparison of the primary and secondary outcomes one year after the injury.

**Discussion:**

The results of this study will provide evidence of the potential benefit of early surgical decompression compared to the current ‘watch and wait’ strategy.

**Trial registration:**

UMIN000006780; NCT01485458

## Background

Acute cervical spinal cord injury (SCI) is one of the most devastating conditions, and can lead to paralysis, sensory impairment and bowel, bladder and sexual dysfunction. In addition, patients frequently suffer from intractable pain caused by neural damage. Individuals with cervical canal stenosis are known to develop cervical SCI even after minor trauma. Cervical canal stenosis may be congenital, but often results from degenerative conditions, such as spondylosis. The SCI patients with canal stenosis are mostly elderly, and usually present with incomplete SCI without bone injury, such as spinal fracture or dislocation. This subgroup of patients has been steadily increasing as the society ages and currently accounts for over 60% of cervical SCIs in Japan [1].

The clinical outcome of patients with incomplete SCI has been considered to be favorable, since patients usually show spontaneous neurologic recovery to some extent. However, the neurological prognosis varies greatly among patients; about half of ASIA C patients remain non-ambulatory six months after the injury [2]. In particular, the clinical outcomes of elderly patients are often suboptimal [3,4]. Therefore, a therapeutic option that leads to a better clinical outcome is urgently needed.

Controversy exists with regard to the efficacy of surgical decompression in the treatment of cervical SCI with preexisting canal stenosis [5,6]. The role of surgery remain unclear, especially in the absence of instability of the cervical spine [7], thus resulting in a significant difference in practice between institutions. A common approach to treating these patients has been to rule out acute instability and then observe the patients’ spontaneous neurological recovery until they achieve a neurological plateau, and only then consider the possibility of surgical decompression, weeks after the initial injury [6]. Our previous retrospective multicenter study showed that the time from injury to surgery was approximately two weeks (median 13.5 days) [8].

The main drawback of this ‘watch and wait’ strategy is that a potential therapeutic window in the acute phase might be missed. The current concept of the pathophysiology of SCI classifies the spinal damage into two stages: primary injury and secondary injury [9]. The primary injury results from the mechanical forces delivered to the spinal cord at the time of the trauma. Secondary injury is a cascade of pathophysiological events including edema, ischemia, inflammation and apoptosis following the initial impact, which develops within minutes to hours following the trauma. There is a growing body of evidence from preclinical or animal studies that early surgical decompression alleviates ‘secondary injury’ and thus results in enhanced neurological and functional recovery [5].

Although numerous studies have been performed to examine the potential benefit of early surgery, the results of these prior clinical studies were mixed, and failed to provide robust support for the hypothesis that early surgery leads to improved outcomes. One small randomized trial of 42 patients showed no benefit to early (< 72 hours) decompression [10]. On the other hand, a meta-analysis of case series showed that early (< 24 hours) decompression was associated with better outcomes compared to both delayed (> 24 hours) and conservative treatment [11]. The results of STASCIS, one of the largest prospective studies of 313 patients, were also in favor of early surgery [12]. The authors of that study reported that early surgery, within 24 hours after injury, is associated with an improved neurological outcome, defined as at least a two grade ASIA Impairment Scale (AIS) improvement at the six-month follow-up examination. However, the difference in the chance of experiencing a one grade AIS improvement between early versus late surgery was not statistically significant.

With such conflicting information in the literature and a lack of high-quality evidence, it remains unclear whether early surgical decompression would result in better neurological and functional recovery. To address this issue, we launched the OSCIS study (Optimal treatment for Spinal Cord Injury associated with cervical canal Stenosis), a randomized, controlled, multicenter trial, in which we will compare the two strategies: early surgery within 24 hours after admission and delayed surgery following at least two weeks of conservative treatment.

## Methods/design

### Trial design

The OSCIS study is a randomized, controlled, parallel-group, assessor-blinded, multicenter study. Patients will be randomly allocated to undergo either early surgery or delayed surgery. The aim of this study is to test the hypothesis that early surgery (within 24 hours after admission) will lead to greater improvements in the motor function compared to delayed surgery (later than two weeks after injury) in patients with acute cervical SCI associated with canal stenosis. The flowchart shown in Figure 1 provides a visual description of the study.

**Figure 1 F1:**
[figure not shown]
Study flowchart.

### Participants

Subjects will be recruited from 36 hospitals in Japan. The list of the participating hospitals with approval from local ethical boards is available as Additional file 1. We will screen all patients with acute traumatic cervical spinal cord injury (at C5 or below) who are admitted to one of the institutions within 48 hours after the injury. The diagnosis of cervical spinal cord injury will be made on the patient’s history, including physical and neurological examinations, and the results of imaging studies, including plain radiographs, magnetic resonance imaging (MRI) and computed tomography (CT).

#### Inclusion criteria

Subjects will be eligible for inclusion if they satisfy the following inclusion criteria:

•aged 20 to 79 years

•without bone injury (spinal fracture or dislocation)

•American Spinal Injury Association (ASIA) impairment Grade C

•cervical canal stenosis due to preexisting conditions, such as spondylosis and ossification of the posterior longitudinal ligament (OPLL)

The presence of cervical canal stenosis will be confirmed by physicians based on the MRI findings obtained on admission. The presence of OPLL will be determined by using plain radiographs or CT. The thickness of the OPLL must be 20% or more of the spinal canal.

#### Exclusion criteria

Subjects will be excluded from enrollment if they meet any of the following conditions:

•unstable medical status

•unable to undergo surgery within 24 hours after admission

•impaired consciousness or mental disorder that precludes neurological examination

•difficulty in obtaining informed consent in Japanese

### Randomization

We will adopt the web-based allocation system using the University Medical Information Network (UMIN), which is one of the data centers that run as a public institution in Japan. By entering the information about the patient, investigators will be able to know the allocation results immediately.

The allocation table, which was created by stratified block randomized by the trial statistician, is registered in the UMIN. The block size is concealed to all investigators involved in this study. We have adopted stratification factors as follows:

•the presence of ossification of the posterior longitudinal ligament (OPLL) (yes/no)

•implementation of high-dose methylprednisolone treatment according to the NASCIS2 protocol (yes/no)

•preexisting gait disturbance due to myelopathy

•degree of canal compromise (50% or more/less than 50% canal compromise)

Preexisting gait disturbance due to myelopathy will be determined by the attending spine surgeon before randomization, based on thorough patients’ history and available medical record. Gait disturbance attributable to other causes (for example, trauma, osteoarthritis, and paralysis after stroke) will be excluded.

Presence of severe canal compromise (50% or more canal compromise) will be assessed by the attending spine surgeon based on mid-sagittal MR images obtained at admission. For patients presented with OPLL, mid-sagittal reconstruction CT images or plain radiographs of the cervical spine will be used to calculate the degree of canal compromise.

### Interventions

Patients will be randomly allocated to undergo either early surgery or delayed surgery.

#### Early surgery

Patients allocated to early surgery will undergo surgery within 24 hours after admission. The time when they enter the operating room will be used as a reference. The principal goal of surgery is to achieve decompression of the spinal cord. The choice of anterior or posterior approach will be left to the surgeon’s discretion. The use of spinal instrumentation will be permitted when needed. The surgery will be performed by or under supervision of a board-certified orthopedic surgeon. The details of the surgical treatment and any perioperative adverse events will be recorded in a web-based predefined form. All patients will receive intensive rehabilitation tailored to the individual and injury-specific factors immediately after surgery.

#### Delayed surgery

Patients allocated to the delayed surgery group will receive conservative treatment consisting of early mobilization and intensive rehabilitation for at least two weeks after the injury. Surgical decompression will be performed by the same team as in the early surgery group at any time later than two weeks after the injury when the physician thinks the timing is appropriate. Physicians will be allowed to treat patients non-surgically as long as the patients can achieve independent ambulation.

#### Other treatments

Apart from the surgical management, all patients will receive appropriate medical support, including permissive or induced hypertensive therapy (mean blood pressure > 85 mmHg) [13]. High-dose methylprednisolone will be used per the discretion of the treatment team according to the NASCIS-2 protocol [1,14,15]. The use or lack of high-dose methylprednisolone must be determined and entered into the web-based database prior to the randomization. Physicians will not be allowed to change or discontinue the administration of methylprednisolone after randomization.

### Primary and secondary outcomes

Participants will be evaluated two weeks, three months, six months and one year after randomization. Table 1 provides an overview of the outcomes that will be used in this study. Physicians and research nurses who are not involved in the patient’s care will assess the outcome at each follow-up examination before the patients see their doctors.

**Table 1 T1:** The timeline of the outcome measures to be collected

		**Follow-up**			
	**Admission**	**2 weeks**	**3 months**	**6 months**	**1 year**
Visit	X^a^	X	X	X	X
Informed consent	X^a^				
Baseline clinical characteristics	X^a^				
Blood analyses	X^a^	X	X	X	X
Magnetic resonance imaging	X^a^				X
Computed tomography	X^a^				
Plain radiographs	X^a^	X			X
Neurological assessment including the ASIA motor score and ASIA impairment scale	X^a^	X	X	X	X
Evaluation of adverse events					
SCIM version 3		X	X	X	X
WISCI II		X			X
SF-36		X			X
EQ-5D		X	X	X	X
NPSI		X			X

X^a^: obtained prior to enrollment; ASIA: American Spinal Injury Association; EQ-5D: EuroQol 5 Dimension; NPSI, Neuropathic Pain Symptom Inventory; SCIM: Spinal Cord Independence Measure; SF-36: Medical Outcomes Study Short Form 36; WISCI: Walking Index for Spinal Cord Injury.

#### Primary outcomes

The primary outcome is a recovery in motor function one year after injury. The assessment will include: 1) the change from baseline to one year after the admission in the ASIA motor score; 2) the total score of the Spinal Cord Independence Measure (SCIM) version 3 and 3) the proportion of patients who regained the ability to walk 100 meters without human assistance.

The ASIA motor score is a 100-point score based on ten pairs of key muscles, each given a five point rating. The SCIM is a validated 100-point disability scale developed specifically for patients with SCI, with an emphasis on daily tasks grouped into three subscales: self-care (20 points), respiration and sphincter management (40 points) and mobility (40 points) [16-18].

#### Secondary outcomes

The secondary outcomes will include: 1) the health-related quality of life as measured by the Medical Outcomes Study Short Form 36 (SF-36) [19,20] and the EuroQol 5 Dimension (EQ-5D) [21]; 2) the neuropathic pain at the injured level and below as assessed by the Neuropathic Pain Symptom Inventory (NPSI) [22] and 3) the walking status as evaluated with the Walking Index for Spinal Cord Injury (WISCI) II [23].

The scores on the SF-36 will be used as a generic measure of the patient health status. The SF-36 comprises eight single subscale scores associated with physical and mental health.

The NPSI is a self-questionnaire specifically designed to evaluate the different symptoms of neuropathic pain. It includes 12 items, each of which is quantified on a (0 to 10) numerical scale. The pain associated with SCI is classified into two categories: at-level pain and below-level pain. Participants will be asked to complete the NPSI separately for pain in the upper extremities (at-level pain) and in the trunk and lower extremities (below-level pain). The WISCI II is a valid 21-level hierarchical scale of walking based on physical assistance, the need for braces and devices, with an ordinal range from 0 (unable to walk) to 20 (walking without assistance for at least 10 meters).

### Adverse events

The occurrence of pre-specified adverse events will be also assessed. Adverse events will be gathered from patients themselves and from the patient record review. The *a priori* defined adverse events are: worsening of paralysis in the upper extremities, worsening of paralysis in the lower extremities, reoperation, use of a respirator (more than one week), tracheostomy, sepsis, pneumonia, acute respiratory distress syndrome, atelectasis, other respiratory complications, wound infection (superficial), wound infection (deep), urinary tract infection, other infections, gastrointestinal bleeding, peptic ulcer, ileus, acute myocardial infarction, other cardiac events, pulmonary embolism, cerebrovascular complication, liver dysfunction/disease, renal dysfunction/disease, delirium, depression, other complications and death.

### Sample size

For this exploratory trial, the sample size was determined primarily based on feasibility. We assumed that it is feasible to enroll approximately 100 patients (50 patients per group) during the planned study period. As there is no valid data to indicate the optimal endpoint to evaluate the neurological and functional recovery of SCI patients, we selected three candidate endpoints as the primary endpoint: 1) the change from the baseline to one year after the admission in the ASIA motor score; 2) the proportion of patients who regained the ability to walk 100 meters without human assistance and 3) the total score of the Spinal Cord Independence Measure (SCIM) version 3.

We need 45 patients per group when the difference to be detected in the ASIA motor score between the groups is 12 points and the common standard deviation is 20. Additionally, we expect that the percentage of ambulatory patients one year after the injury will increase from 50% to 80%. To detect this difference, we need 39 patients for each group. With regard to the SCIM, there are few data that can be used as a basis for sample size calculation. For the reasons above, we set the sample size to be 50 patients per group. All calculations assume an 80% power at a two-tailed significance level of 0.05.

### Statistical methods

All analyses will be based on an intention-to-treat principal, and will be performed with two-sided *P*-values considered significant when they are below 0.05. For a detailed analysis, the statistician will make a statistical analysis plan before the data lock, as indicated below:

1) Primary endpoint:

•ASIA motor score

Calculate the difference one year after the baseline, and compare the two groups using a *t*-test

•The proportion of patients who regained the ability to walk

Calculate the rate of patients who can walk one year after the baseline, and compare the two groups using the chi-square test

•SCIM

Compare the differences in the SCIM after one year.

2) Secondary endpoint:

Compare the differences in the WISCI II, SF-36 and EQ-5D. For the SF-36, we plan to use only the total points, and not to compare each domain.

3) Safety:

We will compare the rates of adverse events between the groups. In particular, in patients that are moved out of the surgical standby group, we will compare the ratio of the occurrence of adverse events with those in the patients in the early operation group.

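### The primary ASIA test, a t-test on one-year change, gives the three interim ASIA scores no role and has no value for a patient without a one-year score

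*Protocol article*

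**What the plan says.** In the protocol article, Statistical methods sets the principle, "All analyses will be based on an intention-to-treat principal", and a two-sided significance level of 0.05. For the ASIA motor score the instruction is "Calculate the difference one year after the baseline, and compare the two groups using a *t*-test". For walking it is "Calculate the rate of patients who can walk one year after the baseline, and compare the two groups using the chi-square test". The detail is deferred, but within this outline: "the statistician will make a statistical analysis plan before the data lock, as indicated below".

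The section Primary and secondary outcomes sets the visits: "Participants will be evaluated two weeks, three months, six months and one year after randomization". In Table 1, the row "Neurological assessment including the ASIA motor score and ASIA impairment scale" is marked at admission and at all four follow-up visits. The primary endpoint is therefore measured at baseline and four more times, and the named test uses the first and last of these five values.

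The sections shown give no rule for a missing one-year value. Death appears only in the list of prespecified adverse events.

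**The concern.** A change to one year cannot be calculated for a patient with no one-year score. Unless a value is imputed first, that patient adds nothing to the ASIA comparison, even if a six-month score is on file. Loss is plausible: patients are aged up to 79, have acute cervical cord injury, and death, sepsis and pneumonia are among the listed events. Unequal loss is plausible too, because the arms differ in the timing of surgery and some delayed-arm patients may have none.

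Two things are at stake. The first is power, since the planned 50 per arm is only a little above the 45 that the ASIA calculation needs. The second is bias, if those lost are recovering worse and loss differs by arm.

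This is more than a detail left open, because the single-time-point t-test is what the analysis plan is told to follow.

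**Working it through.** **Inputs from the Sample size section:** difference 12 points, SD 20 (so d = 12/20 = 0.6), 80% power, two-sided 0.05, 45 per group needed, 50 per group planned. **Assumed, because the documents give no figures:** the loss rate, the correlation ρ between six-month and one-year values, and how strongly loss depends on the six-month score.

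**1. The plan's own figure.** The exact t-based sample size for d = 0.6 is 44.6, so 45 per group. The stated figure is right. Power at 50 per group is 84.4%. The margin absorbs 1 − 45/50 = 10% loss.

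**2. Power.** With a fraction m lost, the t-test on observed one-year values has n₁ = 50(1 − m) per arm. If every lost patient has a six-month score, a likelihood-based model over visits is worth about n₁/(1 − ρ²m) per arm.

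| Loss m | n₁ | t-test power | model, ρ = 0.5 | model, ρ = 0.7 | model, ρ = 0.9 |
|---|---|---|---|---|---|
| 10% | 45.0 | 80.4% | 46.2 → 81.4% | 47.3 → 82.3% | 49.0 → 83.6% |
| 15% | 42.5 | 78.0% | 44.2 → 79.6% | 45.9 → 81.1% | 48.4 → 83.2% |
| 20% | 40.0 | 75.5% | 42.1 → 77.7% | 44.3 → 79.8% | 47.7 → 82.7% |

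Example at 15% loss and ρ = 0.9: 42.5/(1 − 0.81 × 0.15) = 42.5/0.8785 = 48.4. Patients lost before six months leave weaker predictors, so the real gain would be smaller. Any gain from adjusting for baseline and the stratification factors is not counted.

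**3. Bias of an observed-values comparison.** Suppose the arms truly do not differ, low six-month scorers are likelier to be lost, and loss is 20% in one arm and 5% in the other. Then bias = ρ × 20 × (difference between arms in the mean standardised six-month score of those retained).

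- Logistic loss, slope 0.5 per SD: 0.097 − 0.025 = 0.071 (from unrounded means). Bias is 1.0 point at ρ = 0.7 and 1.3 at ρ = 0.9.
- Slope 1: 0.174 − 0.048 = 0.126. Bias is 2.3 points at ρ = 0.9.
- Slope 1.5: 0.227 − 0.066 = 0.161. Bias is 2.9 points at ρ = 0.9.
- Ceiling, where exactly the lowest scorers are lost: 0.350 − 0.109 = 0.241. Bias is 4.3 points at ρ = 0.9.

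The range is about 1 to 4 points, and the arm with more loss looks better. A model that uses the six-month score removes this bias only because loss was assumed to depend on that observed score.

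**4. Why the walking denominator should be stated.** Suppose 50% of those randomised walk at one year in both arms, and deaths are 12% and 4%. With everyone in the denominator, the arms are equal. With the dead left out, the rates are 0.50/0.88 = 56.8% and 0.50/0.96 = 52.1%, a spurious gap of 4.7 points. The protocol does not state such an exclusion; the example shows only that the denominator matters.

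**The case against.** A reader might infer that the plan contradicts itself by claiming intention-to-treat while prescribing completer analyses. The document does not support this. No section limits the analysis to patients with a one-year value. A t-test can follow imputation, and a chi-square test can keep every randomised patient by counting the dead or lost as not walking. The phrase about the walking rate describes who is counted as a success and does not state the denominator; under intention-to-treat, all randomised patients is the natural one. Rules for missing data and deaths are commonly left to the analysis plan, so their absence from this article is not an error. All of this stands.

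It is also fair to say that the trial is described as exploratory with a feasibility-based size, that a t-test on change at one fixed time is valid, and that 50 per arm keeps 80% power up to 10% loss without any model. The power gain is modest, and a bias of 3 points or more needs strong selection as well as a fourfold imbalance in loss. This limits the size of the point. It does not remove it: the named test gives collected primary-endpoint data no role, and the analysis plan is tied to that outline.

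Finally, a mixed model does not solve the problem of deaths. It gives a patient who dies an implicit hypothetical one-year score.

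**Conclusion.** The point holds as a weak choice of primary ASIA analysis, not as a breach of intention-to-treat or a sample-size error. Inferring from the test names that deaths and drop-outs are excluded goes further than the text.

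The power lost by using only observed one-year values, relative to the model, is about 1 to 3 percentage points at 10% loss, 2 to 5 at 15% and 2 to 7 at 20%, for correlations of 0.5 to 0.9 and a six-month score on every lost patient. With 20% against 5% loss, bias is about 1 to 4 points for correlations of 0.7 to 0.9, or roughly 8% to 36% of the 12-point target. All of these rest on assumed loss rates, correlations and selection strength. With nearly complete one-year follow-up, the interim scores would change little.

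**What to change.** Replace the t-test with a mixed model for repeated measures on ASIA change at two weeks, three months, six months and one year, in all randomised patients with follow-up data. Include treatment-by-visit, baseline-by-visit and the four stratification factors, and take the treatment contrast at one year as the primary result. Add a sensitivity analysis for deaths and for departures from missing at random.

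In the analysis plan, confirm that the walking rate uses all randomised patients, with deaths counted as not walking and a sensitivity range for living patients lost to follow-up.

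The cost is wording and a little more analysis work, with no new data. The article reports the trial as still recruiting, and the analysis plan is due before data lock, so on that timetable the change can precede the analysis. The downsides are a missing-at-random assumption, a less simple analysis than a t-test, and the hypothetical score implied for patients who die.

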## Discussion

Despite intensive basic and clinical research, an effective treatment for cervical SCI has not been established. In the presence of preexisting canal stenosis, the role of surgical decompression and its optimal timing continue to be subjects of intense debate. Addressing the issue of the timing of surgical intervention is critical in that, if the timing of surgery has no effect on the patient’s outcome, then all patients can initially be treated non-surgically and surgery can be delayed for weeks or even months after the injury without compromising the patient’s recovery [6]. On the other hand, if early surgical decompression is proven to be beneficial, drastic changes in the medical service system, including logistics, should be made to ensure that all SCI patients receive early surgery.

In conducting clinical studies on SCI, the heterogeneity of the study population can be a major obstacle, especially in the acute phase. SCI patients vary greatly in the severity of paralysis and neurological prognosis. Clinical studies including patients with various degrees of neurological injury may have insufficient power. Therefore, in this study, we will focus on patients with ASIA C status. In a recent review, the consensus of experts was that it is reasonable to consider early surgical decompression in patients with profound neurologic deficit (ASIA C) and spinal canal stenosis without fracture or instability. On the other hand, those with a less severe deficit (ASIA D) can be treated with initial observation with surgery potentially performed at a later date [6]. We will exclude patients with ASIA B status, because these patients are often difficult to distinguish from ASIA A patients at the time of admission.

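### The ASIA motor score primary analysis is fixed as an unadjusted t-test on change; adjusting for the admission score and the stratification factors would use data already collected, is essentially never less precise, and would correct chance baseline imbalance properly

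*Protocol article*

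**What the plan says.** The Sample size section of the protocol article lists, among three candidate primary endpoints, "the change from the baseline to one year after the admission in the ASIA motor score". For its analysis, the Statistical methods section reads "Calculate the difference one year after the baseline, and compare the two groups using a" *t*-test. No covariate, adjusted model or sensitivity analysis is named. A statistical analysis plan is to be written before data lock, but along the lines given in that section, so the test itself is settled in the protocol.

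Table 1 has a row "Neurological assessment including the ASIA motor score and ASIA impairment scale", marked at admission (obtained before enrollment) and at two weeks, three months, six months and one year. The Randomization section stratifies on OPLL, high-dose methylprednisolone, preexisting gait disturbance and degree of canal compromise. The admission motor score is not a stratification factor.

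The Sample size section asks for 45 patients in each arm, at 80% power and two-sided alpha 0.05. The inputs behind that figure are: "the difference to be detected in the ASIA motor score between the groups is 12 points and the common standard deviation is 20". The section then settles the size: "we set the sample size to be 50 patients per group".

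**The concern.** Comparing mean change is the same as adjusting for baseline with the slope fixed at 1. There is no reason to expect exactly 1. The Primary outcomes section notes that "The ASIA motor score is a 100-point score based on ten pairs of key muscles", so the scale has a ceiling, and patients who start higher have less room to gain. Where the true slope is not 1, two things follow. Some outcome variance that the admission score could explain stays in the error term. And a chance difference in admission score between the arms, which the stratification does not specifically prevent, is removed by the wrong amount.

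The test also ignores the four stratification factors. If they are prognostic, an unadjusted standard error tends to be too large for a randomization that balanced them.

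What is at stake is precision and robustness on one of three primary endpoints, in a trial whose size was set mainly by feasibility. Lost precision cannot easily be recovered by recruiting more patients.

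**Working it through.** **Inputs from the protocol.** Difference 12, common SD 20, two-sided alpha 0.05, 80% power, 45 per group needed, 50 per group planned, 1:1 allocation.

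**Inputs that the protocol does not give, hence assumed.**
- The correlation rho between admission and one-year score: 0.3 to 0.7.
- The ratio k of baseline SD to one-year SD: 0.5, 0.7 and 1.
- That the SD of 20 refers to change. The Sample size section does not say whether it refers to change or to the score.

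**Step 1: the plan's own figure.** The standardized difference is 12/20 = 0.6. The noncentral *t* calculation gives 44.59, so 45 per group (80.4% power). At 50 per group, power is 84.4%. The stated sample size is reproduced.

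**Step 2: variance of ANCOVA relative to the change score.** Set the one-year SD to 1 and the baseline SD to k.
- Change-score variance: 1 + k² − 2k·rho.
- ANCOVA variance: 1 − rho².
- Ratio: (1 − rho²)/(1 + k² − 2k·rho). This equals 1 − r², where r is the correlation of change with baseline, so it cannot exceed 1.
- At k = 1 it reduces to (1 + rho)/2.
- The slope is beta = rho/k.

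**Step 3: power at 50 per group**, with the change SD held at 20 and the ANCOVA SD equal to 20·√ratio. The small loss of degrees of freedom is ignored, and the stratification factors are left out.

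| k | rho | beta | ratio | power |
|---|---|---|---|---|
| 1 | 0.3 | 0.30 | 0.65 | 96% |
| 1 | 0.5 | 0.50 | 0.75 | 93% |
| 1 | 0.7 | 0.70 | 0.85 | 90% |
| 0.7 | 0.3 | 0.43 | 0.85 | 90% |
| 0.7 | 0.5 | 0.71 | 0.95 | 86% |
| 0.7 | 0.7 | 1.00 | 1.00 | 84% |
| 0.5 | 0.3 | 0.60 | 0.96 | 86% |
| 0.5 | 0.5 | 1.00 | 1.00 | 84% |
| 0.5 | 0.7 | 1.40 | 0.93 | 87% |

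With equal SDs the gain over 84% is about 5 to 11 percentage points. With a narrower baseline it is about 0 to 5. If the baseline SD exceeds the one-year SD, the gain is larger than in the first three rows.

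**Step 4: the other reading of SD 20.** If 20 is the SD of the score at both times, the change SD is 20·√(2(1 − rho)) and the ANCOVA SD is 20·√(1 − rho²). By normal approximation at 50 per group:
- rho 0.3: change SD 23.7, power 72%; ANCOVA SD 19.1, power 88%.
- rho 0.5: 85% against 93%.
- rho 0.7: 97% against 99%.

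**Step 5: chance imbalance.** A baseline difference d shifts the change comparison by (beta − 1)d. With an assumed baseline SD of 15, the standard error of d at 50 per group is 15·√(2/50) = 3.0 points, and 1.96 × 3.0 = 5.88. The shift is then −4.1 points at beta 0.3, −2.9 at 0.5, −1.8 at 0.7 and 0 at 1, against a target difference of 12. For an assumed baseline SD of 10 or 20 the shift at beta 0.5 is −2.0 or −3.9.

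**The case against.** The strongest reply is that nothing here is an error. The endpoint is defined as change, the test is on change, and the sample size matches the test. The *t*-test is unbiased over randomization. Power at the planned size already exceeds 80% if SD 20 is the SD of change, and the protocol calls the trial exploratory. All of that stands. A reader might infer that the sample size is wrong or the conclusions invalid; the documents support neither.

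The second reply concerns size. The larger gains need equal SDs at baseline and one year. Entry is restricted to ASIA grade C while outcomes are expected to differ widely, so a narrower spread at baseline is plausible, and the gain may then be close to nil. This also stands: no single power figure can be offered as the loss. Nor does the Discussion's remark on heterogeneity show a wide baseline spread here. It concerns SCI patients in general and is given as the reason for restricting entry.

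A reader might also infer that chance imbalance goes wholly uncorrected. It does not: subtracting baseline does correct it, but with a slope of 1 whatever the data say. The direction of the error is not fixed either, since beta can exceed 1 when the baseline is narrow.

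The third reply is that covariates belong in the analysis plan. This is only a partial answer, because the protocol names the test and says that the plan will follow it.

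**Conclusion.** The point holds as a weakness of efficiency and robustness. The protocol commits to an unadjusted comparison of change when a better estimator of the same effect is available from data already scheduled. Apart from a trivial loss of degrees of freedom, ANCOVA is never less precise here, so there is little to lose and possibly much to gain.

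The size is uncertain and depends on quantities that the documents do not give. Under the assumptions above, power at 50 per group would be 90–96% with equal SDs, or 84–90% with a baseline SD of 0.5 to 0.7 of the one-year SD, against 84.4% for the *t*-test. Only the pattern is firm: the precision gain from the admission score vanishes when change is uncorrelated with baseline and grows with that correlation. The extra gain from the stratification factors has not been quantified.

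**What to change.** Before data lock, and before outcomes are seen by arm, specify as the primary analysis of this endpoint an ANCOVA of the one-year ASIA motor score (or, equivalently for the treatment effect, of change) on arm, admission ASIA motor score and the four stratification factors. Report the adjusted mean difference with its 95% CI. Keep the *t*-test on change as a supportive analysis. The Sample size section should also say whether the SD of 20 refers to change or to the score.

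The cost is a short edit to the analysis text. No new data, visits or patients are needed, and the planned 50 per group can stay. Fixing the covariates in advance also removes the temptation to adjust only if the arms turn out to differ at baseline. A model that uses the earlier visits as well would be a separate decision: it is a repeated-measures model with its own covariance and missing-data assumptions, and is not part of this change.
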